**Figure 1 fig1:**
[figure not shown]
Schematic representation of the study.

A participant in the study may withdraw their consent at any time, without the need to provide any justification. This decision will not entail any liability or negative consequences for the participant. Individuals who choose to withdraw will not undergo further follow-up and will not be replaced. The investigator reserves the right to withdraw a participant from the study if it is determined that the participant can no longer comply with the study requirements or if any of the procedures are deemed potentially harmful to the participant’s wellbeing. Any data collected from participants prior to withdrawal will be retained and included in the analysis; however, no additional data will be collected after the point of withdrawal. Participants may be excluded or withdrawn from the study, even after sample collection, if they meet any of the following criteria:

Occurrence of an adverse event that, in the investigator’s judgment, warrants withdrawal.Protocol deviation that compromises the interpretation or scientific validity of the study results.Medical decision.Voluntary decision by the participant to discontinue participation.Loss to follow-up.

During the sample collection period, participants will continue attending their regular medical visits and receiving standard clinical follow-up.

To monitor compliance with the intervention, participants, with the assistance of their study partner, will complete a supplement intake tracker. This will consist of a daily diary (paper-based) where supplement intake, timing, and any missed doses will be recorded. Returned bottles/sachets will also be counted at each follow-up visit, and weekly phone calls will be conducted to reinforce adherence and address potential barriers. Adherence will be calculated as the percentage of prescribed doses consumed. Participants with ≥80% adherence will be considered compliant.

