### Allocation

2.5

For the nutritional intervention study, patients with AD will be randomly assigned to two groups (*n* = 30 each) using the free randomization software OxMar (26). Randomization will not be stratified by study site. However, the study site will be included as a covariate in the statistical models to control for its potential effect as a confounding variable. The control group will receive a standard nutritional supplement commonly used in patients with AD (Souvenaid^®^, Nutricia, Madrid, Spain), and dietary recommendations will be provided if their usual intake does not meet the established nutritional goals for this population. The intervention group will receive the newly designed supplement, along with tailored dietary recommendations. The group assignment will be performed by the team of neurologists. Supplement blinding in terms of format, flavor, odor, etc., is not planned in this study. Supplements will be labeled as either “A” or “B,” and participants will be informed that they are taking a supplement but will not know whether it is the standard or the “*ad hoc*” formulation. To eliminate bias, the researchers conducting the experiments and performing the analyses will remain blinded to group allocation. Baseline demographic and clinical information will be collected for participants who discontinue the study, along with available data on health status, adverse events, and primary efficacy outcomes.

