### Statistical analysis

2.21

The analysis of the obtained data will be carried out using the statistical software SPSS version 29.0. The mean and standard deviation, or the median and interquartile range, will be used to describe each parameter, depending on the data distribution. The assumption of normality will be assessed using the Shapiro–Wilk test. All continuous outcomes will be analyzed using linear models adjusting for the baseline value of the outcome and a set of covariates: age, sex, education level, comorbidity burden, concomitant medication, physical activity level, nutritional status, and perceived stress. Study site will be included as a fixed effect. For outcomes with repeated measures (e.g., pre/post within participants), we will use linear mixed-effects models with a random intercept for participant and treatment group (personalized supplement vs. control) as the main fixed effect. Where a single post-intervention endpoint is analyzed, an ANCOVA (post value as dependent variable; treatment as factor; baseline outcome and covariates as regressors) will be used. An intention-to-treat (ITT) approach will be employed to evaluate the effectiveness of the intervention. The ITT analysis will include all participants initially randomized, regardless of whether they completed the intervention as planned, withdrew, or deviated from the protocol. For gut microbiota analysis, RStudio (v. 1.4.1106, RStudio, 2022) will be used. The phyloseq R package (51) will be employed to compare different estimates of alpha diversity and to plot the relative abundance of microbial groups. The vegan R package (52) ^1^will be used to compute beta diversity, i.e., inter-sample diversity, visualized through Principal Coordinates Analysis (PCoA) based on the Bray–Curtis dissimilarity index. The significance and effect of treatments on the bacterial community (beta diversity) will be evaluated using PERMANOVA implemented in the vegan package. Differences will be considered statistically significant when the *p*-value is less than the alpha level (0.05). For microbiome, functional profiles and untargeted metabolomics, we will use MaAsLin2, a multivariable linear modeling framework designed for meta-omics data analysis (53) with appropriate normalization/transformations, adjusting for the same covariates listed above. Participant ID will be specified as a random effect for longitudinal analyses. For multiple comparisons, the Benjamini–Hochberg correction will be applied to control the false discovery rate. To address multiplicity, two complementary approaches will be applied depending on the type of outcomes. For a small number of primary or key secondary outcomes (e.g., plasma LPS, total SCFAs), we will apply the Bonferroni correction. For high-dimensional exploratory domains (microbiota taxonomic and functional profiles, untargeted metabolomics, and dietary intake variables), *p*-values will be adjusted using the Benjamini–Hochberg procedure to control the false discovery rate (FDR).

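### Sections 2.2, 2.5 and 2.21 conflict on randomised participants who deviate or discontinue, so the ITT comparison would in effect rest on those with a T=3 sample

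*Protocol article*

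**What the plan says.** **Section 2.21, Statistical analysis**, defines the population: "The ITT analysis will include all participants initially randomized, regardless of whether they completed the intervention as planned, withdrew, or deviated from the protocol". Pre/post outcomes go into a linear mixed model with a random intercept per participant. Where one post-intervention endpoint is analysed, the model is an ANCOVA with the post value as the response.

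**Section 2.2, Interventions** (text after Figure 1), governs leaving the study.
- On voluntary withdrawal: "Individuals who choose to withdraw will not undergo further follow-up and will not be replaced".
- The investigator may also withdraw someone "if it is determined that the participant can no longer comply with the study requirements".
- On data: "Any data collected from participants prior to withdrawal will be retained and included in the analysis", but "no additional data will be collected after the point of withdrawal".
- Then: "Participants may be excluded or withdrawn from the study, even after sample collection, if they meet any of the following criteria". One listed criterion is "Protocol deviation that compromises the interpretation or scientific validity of the study results". The others are adverse events, medical decision, the participant's own decision and loss to follow-up.

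**Section 2.5, Allocation**: "Baseline demographic and clinical information will be collected for participants who discontinue the study". The same sentence extends this to available health, safety and primary efficacy data.

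Section 2.2 gives the trial one measurement before the intervention (T=2) and one after it (T=3).

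**The concern.** Two things do not fit together. First, section 2.21 keeps deviators in the analysis, while section 2.2 makes a deviation a ground for exclusion, even once samples have been taken. Second, section 2.2 stops data collection at withdrawal, while section 2.5 speaks of collecting data, efficacy included, on people who discontinue. Site staff cannot tell from this whether to seek a T=3 sample from someone who has come off the supplement.

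This matters because loss could depend on arm. The two products are not matched in format, flavour or odour (section 2.5), and adverse-event reporting gives particular attention to gastrointestinal symptoms (section 2.10). The neurologists make the group assignment, and the researcher blinding in section 2.5 is stated only for those running the experiments and analyses. If the people without T=3 differ between arms in ways related to outcome, the comparison loses the protection of randomisation while still being labelled ITT. Section 2.4 lists estimating effect sizes and gathering data to power a definitive trial among the pilot's aims, so a distorted estimate would carry forward. A T=3 sample that was never taken cannot be recovered later.

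**Working it through.** **1. The plan's own figures (section 2.4).** Effect size 0.51 / 0.6533 = 0.7806; two-sided alpha 0.05; power 0.80. The stated formula gives 2 × (1.960 + 0.842)² / 0.7806² = 25.76 per group, which rounds up to 26; the plan states 25. The plan's 30 per arm is 25 × 1.20. These small differences do not bear on this point. The figures only set its scale.

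**2. Outcomes at risk.** 60 × 0.20 = 12 participants, leaving 48 (24 per arm if the loss is even). Twelve is an upper figure, since not every dropout need lack T=3.

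**3. The sections side by side.**

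| Randomised participant | Section 2.21 | Section 2.2 | Section 2.5 | T=3 outcome |
|---|---|---|---|---|
| Takes too little supplement but stays | In ITT | Below 80% adherence is not counted as compliant; not removed for that alone | – | Yes |
| Deviates, then excluded after sampling | In ITT | Data before *withdrawal* kept; use after *exclusion* not stated | – | May exist; use unclear |
| Comes off supplement and is withdrawn before T=3 | In ITT | Earlier data kept; nothing further | Available efficacy data collected | No under 2.2, unclear under 2.5 |
| Withdraws consent before T=3 | In ITT | Earlier data kept; nothing further | As above | No |

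The second and third rows are where the sections pull apart.

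**4. What the models can use.** ANCOVA on the post value needs T=3. The mixed model keeps T=2 rows, but one pre-treatment value says little about a treatment effect. A simulation (30 per arm, no true effect, pre/post correlation 0.5, 20% of each arm without T=3, 400 runs) gave:
- Loss at random: SD of the treatment-by-time estimate 0.279 with all rows and 0.287 using only participants with T=3, a gain of (0.287 − 0.279) / 0.287 = 2.8%.
- Loss related to a poor T=3 value in the experimental arm only: mean estimate 0.20 SD by ANCOVA on those with T=3 and 0.19 SD by the mixed model with all rows, against 0.02 SD with full follow-up. The mixed model without the leavers' T=2 rows gave 0.13 SD, so those rows did not repair the bias.

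**5. Size of a possible bias.** Let d be the share lost in an arm and x the amount by which its stayers exceed its leavers, in SD. An unadjusted comparison of stayers is biased by d_E·x_E − d_C·x_C.
- Equal loss unrelated to outcome (x = 0): 0.
- Assumed 30% versus 10%, x = 0.5 in both arms: (0.30 − 0.10) × 0.5 = 0.10 SD.
- The same split, x = 1.0: (0.30 − 0.10) × 1.0 = 0.20 SD.

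The split and x are assumptions; the document gives neither. Equal dropout rates alone do not guarantee zero: the simulation in step 4 lost 20% from each arm.

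**6. Precision.** At the plan's effect size, power by normal approximation is 85.6% with T=3 on 30 per arm, 81.8% on 27, 77.2% on 24 and 71.6% on 21. That effect size is the AD-versus-healthy difference in *Odoribacter*, not a supplement effect, so these figures only show the scale of the information lost.

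**The case against.** The strongest reply is that the sections can be read together. Section 2.2 keeps and analyses data collected before withdrawal, and its list concerns exclusion from the *study*. On that reading removal ends participation, and what was already collected is analysed as randomised. In section 2.5, *available* may mean only data already in hand at discontinuation. Missing outcomes are then a missing-data problem and do not contradict the ITT definition. Much of this stands: a reader might infer that section 2.2 deletes deviators from the analysis set, but no sentence says so. What remains is that the retention sentence speaks of withdrawal only, while the next paragraph adds exclusion, even after sampling, to protect the validity of the results. The text leaves open what happens to those samples.

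A reader might also infer that the ITT analysis becomes a completers analysis. The document does not support that. Poorly adherent or deviating participants who stay give T=3 and are analysed, and the mixed model keeps T=2 rows. The set that drives the comparison is participants with T=3, not those who completed treatment.

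Three further points stand. The products are labelled A or B, participants are not told which is the standard one, and laboratory and analysis staff are blinded, which limits some routes to differential loss. How missing T=3 values are handled, and any per-protocol set, may be in a statistical analysis plan not shown and are not counted here. The trial is an exploratory pilot, which lowers the stakes without settling what the sections mean.

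**Conclusion.** The concern holds as a conflict of wording with a practical consequence. Sections 2.2, 2.5 and 2.21 do not agree on what happens to randomised participants who deviate or discontinue. Followed as written, section 2.2 forgoes outcomes that the ITT analysis in section 2.21 needs. With a single post-intervention visit, the treatment comparison is in effect limited to participants with T=3, losing up to 12 of 60 at the planned dropout.

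Whether this biases the result cannot be told from the document. The range runs from zero to 0.10–0.20 SD under the assumed unequal loss and leaver difference. It should not be expressed as a share of the 0.78 planning effect, which belongs to a different contrast. Nor are all 12 recoverable: some will have withdrawn consent or been lost to follow-up, and the document does not say how many.

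Given the pilot aims, this should be fixed, preferably before the intervention starts, but it does not invalidate the design.

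**What to change.** 1. Reconcile sections 2.2, 2.5 and 2.21 so that they give one rule on data after discontinuation.
2. State that *excluded* never means removing a randomised participant, or samples already collected, from the ITT set.
3. Separate discontinuing the supplement from withdrawing from the study. The reasons for stopping the product stay as they are.
4. Seek T=3 stool and blood from everyone who has not withdrawn consent to follow-up, whether or not they are still taking the supplement.

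The cost is a revision of wording, with whatever ethics approval that needs, and T=3 sampling of a few participants already enrolled: at most about 12 at the planned dropout, and fewer once consent withdrawals and losses to follow-up are set aside. Participants or their study partners may find the extra visit a burden, and some will decline.

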	Perceived Stress Scale (PSS-10)

### Sample size calculation

2.4

To calculate the sample size, the method used to test the association between the abundance of a microbiota taxon and exposure to a variable or group of variables was applied (23). The bacterial genus *Odoribacter* was selected for this purpose, as its abundance has shown a significant role in predicting AD (24). The mean and standard deviation of the relative abundance of this genus were 0.26 ± 0.42 in healthy individuals and 0.77 ± 0.77 in patients with AD, according to data obtained directly from the authors of Liang et al. (25). The pooled standard deviation was 0.6533, and the calculated effect size was: (0.77–0.26)/0.6533 = 0.7806. Considering this effect size, and assuming a significance level (*α*) of 0.05 and statistical power (1 − *β*) of 0.80, the formula used for calculating the sample size was: 
n=[2×(z₁⋅α/2+z₁⋅β)2]/(effect size)2
. Substituting the values yields a required sample size of 25 individuals per group. To account for an estimated 20% dropout rate, the final sample size was adjusted to 30 participants per intervention group. Accordingly, the cross-sectional stage (stage 1) will be conducted with *n* = 60 participants per group, which will provide robustness to detect differences between healthy individuals and patients with AD. In the subsequent intervention phase, which will be carried out exclusively in patients with AD, these 60 individuals will be randomized into two arms: one receiving the designed supplement and the other a standard supplement. The aims of this pilot intervention are to: (i) estimate trends and effect sizes of the intervention on the microbiota and clinical parameters, (ii) evaluate the feasibility and acceptability of the intervention protocol in this vulnerable population, and (iii) collect preliminary data to power a future definitive randomized controlled trial. The intervention will last 3 months, as the aim is to obtain preliminary results in a pilot context.

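### Section 2.4 rounds 25.76 down to 25 and inflates for 20% dropout by multiplying, so 30 per arm leaves 24 completers and about 75–77% power, not 80%, for a standardised difference of 0.78

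*Protocol article*

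**What the plan says.** The sample size section (2.4) rests on the relative abundance of one genus, given as "0.26 ± 0.42 in healthy individuals and 0.77 ± 0.77 in patients with AD". With a pooled standard deviation of 0.6533 this becomes an effect size of 0.7806. The error rates are set by "assuming a significance level (*α*) of 0.05" and "statistical power (1 − *β*) of 0.80", and the formula, as extracted from the PDF, is "n=[2×(z₁⋅α/2+z₁⋅β)2]/(effect size)2". The result is stated as: "Substituting the values yields a required sample size of 25 individuals per group". The next step reads: "To account for an estimated 20% dropout rate, the final sample size was adjusted to 30 participants per intervention group".

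Stage 1 then takes 60 participants per group, AD and healthy. For the intervention stage the section says that "these 60 individuals will be randomized into two arms", and section 2.5 (Allocation) fixes 30 in each arm. Section 2.2 (Interventions) leaves the time between baseline characterisation (T = 0) and the start of the intervention (T = 2) open, depending on recruitment, sequencing and data processing. On withdrawals it says: "Individuals who choose to withdraw will not undergo further follow-up and will not be replaced".

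**The concern.** Two steps in section 2.4 do not hold together. The formula does not return 25 when a required size is rounded up. The dropout step also fails its own purpose: the number left after the stated 20% loss is below the number the section says is needed. The section justifies the size of the intervention arms by a formal 80% power statement, and that statement is not met on the plan's own inputs.

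A third provision is unsupported. Having 30 per arm at randomisation requires every one of the 60 patients characterised at T = 0 to be available and willing at T = 2, after an interval of unstated length during which the supplement is designed. Those who withdraw are not replaced. No allowance for loss in that interval is stated separately.

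What is at stake is the accuracy of the stated size and power for the between-supplement comparison, and how realistic the planned number randomised is. The stage 1 comparison is not at stake.

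**Working it through.** **Inputs, all from section 2.4:** effect size d = 0.7806; two-sided alpha 0.05 (the formula uses alpha/2), so z = 1.960; power 0.80, so z = 0.842; dropout 20%; 30 per intervention arm; 60 per group in stage 1.

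**1. The plan's effect size.** (0.77 − 0.26)/0.6533 = 0.7807, which agrees with the stated 0.7806 apart from the last digit. The pooled SD itself cannot be checked. Equal weights would give √((0.42² + 0.77²)/2) = 0.620, so 0.6533 implies unequal source groups whose sizes the article does not give. It is accepted here as stated.

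**2. The plan's 25.** n = 2 × (1.960 + 0.842)² / 0.7806² = 25.76 per group. Truncated, this is the stated 25. Rounded up, it is 26. With the t distribution, 27 are needed. Power at 25 per group is 78.8% by the plan's normal formula and 77.2% by the t test. At 26 the normal formula gives 80.4%.

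**3. The plan's 30.** 25 × 1.2 = 30 reproduces it. The check is what remains after the stated loss: 30 × (1 − 0.20) = 24, below both 25 and 26. Thirty per arm keeps 25 only if dropout is at most 1 − 25/30 = 16.7%. To retain n after a loss of 20%, divide by 0.8:

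- from 25: 25/0.8 = 31.25, so 32 per arm (64 in total);
- from 26: 26/0.8 = 32.5, so 33 per arm (66 in total).

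**4. Power with 24 completers per arm, two-sided 0.05, standardised difference 0.7806.** Normal formula: Φ(0.7806 × √(24/2) − 1.960) = Φ(0.744) = 77.2%. Noncentral t: 75.4%.

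**5. Stage 1, AD versus healthy.** With 60 per group, power for 0.7806 is 99.0% (normal) or 98.9% (t). With 48 per group (60 less 20%) it is 96.9% (normal).

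**6. Loss between T = 0 and randomisation.** The article gives no rate. The rows below are *assumed scenarios*: a loss before randomisation, followed by a further 20% during the intervention.

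| Assumed loss before randomisation | Randomised per arm | Completers per arm | Power, normal | Power, t test |
|---|---|---|---|---|
| 0% | 30 | 24 | 77.2% | 75.4% |
| 5% | 28.5 | 22.8 | 75.0% | 73.1% |
| 10% | 27 | 21.6 | 72.8% | 70.7% |
| 20% | 24 | 19.2 | 67.7% | 65.3% |

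If the 20% is instead meant to cover everything from T = 0 to T = 3, then 60 × 0.8 / 2 = 24 complete per arm, and the 0% row applies.

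**The case against.** The case against making much of this has several parts.

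- **The rounding is one patient.** That is true: power at 25 is still 78.8% by the plan's formula. On its own it would be a trivial correction. The dropout step is the more material error, because it fails whichever way 25.76 is rounded.
- **The intervention is a pilot.** Section 2.4 lists estimation, feasibility and data for a later trial as its aims, and the Discussion disclaims definitive outcomes. A drop from 80% to 75–77% changes no decision. This limits the consequence. It does not remove the error, because the section supports its arm size with a formal power calculation.
- **The planned analysis differs from the calculation.** Section 2.21 uses baseline-adjusted models under intention to treat, and the calculation is for an unadjusted two-group comparison. Adjustment might recover some power, but the article gives no correlation from which to say how much. The stated 80% was not derived that way.
- **The effect size does not belong to the randomised contrast.** This stands. The 0.7806 is an AD-versus-healthy difference, so no power figure built on it is the trial's power for a documented supplement effect. Any restated figure has to say so.

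A reader might also infer that the design as a whole delivers only about 65–77% power for its own effect size. The documents do not support that. The contrast that produced the effect size is tested in stage 1 at about 99% power. The 65% end needs an assumed 20% loss before randomisation, a further 20% dropout and a t test, and the article states no such pre-randomisation rate. Nor does it attach a period to its 20%, so it cannot be asserted that the allowance covers only the three-month phase. The 1.5 years mentioned in section 2.3 (Outcomes) is attached to the healthy-versus-AD comparison and is not defined as the wait from T = 0 to T = 2.

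**Conclusion.** The arithmetic error is established from the article's own inputs. The formula gives 26 per group, and 20% dropout requires 33 per arm (32 if 25 is kept). The planned 30 leaves 24 completers per arm, with 77% (normal) or 75% (t) power in place of 80%. These figures rest only on the stated alpha, effect size and dropout rate. They apply to the two-arm intervention comparison at a standardised difference of 0.78, which is not an estimate of what the supplement would do.

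It is also established that 30 per arm presupposes no loss between baseline characterisation and randomisation, with an open interval and no replacement. How much power that would cost cannot be derived from the article. Figures such as 71% at 10% loss or 65% at 20% loss (t test) are illustrations under assumed rates. The shortfall is modest and the study is a pilot, but the stated size and power are wrong and should be corrected.

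**What to change.** In section 2.4:

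- Change 25 to 26 and give the dropout-inflated requirement as 33 per arm.
- If 60 patients are kept, say plainly that 30 per arm with 20% dropout leaves 24 completers per arm and about 75–77% power for an *assumed* standardised difference of 0.78. Add that this value is the AD-versus-healthy difference and not an estimate of the supplement effect.
- State whether the 20% covers the whole period from T = 0 to T = 3 or only the three-month intervention.

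In sections 2.4 and 2.5, give the number randomised as up to 30 per arm in place of a fixed 30. If power under further loss before randomisation is shown, label it as an assumed scenario.

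The cost is a few reworded sentences and no extra enrolment. Restoring 80% by the plan's formula would be a different choice: 66 patients randomised, and more than that characterised at T = 0 if losses before randomisation are expected (66/0.9 gives 74 at an assumed 10%, 66/0.8 gives 83 at an assumed 20%).
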